## Introduction

Atrial Fibrillation (AF) is the most common arrhythmia, and its significant increase in prevalence has led to heightened risks of heart failure and stroke within the population. It is projected that by 2050, at least 72 million individuals in Asia will be diagnosed with AF, with approximately 3 million potentially experiencing AF-related strokes. Furthermore, AF imposes a considerable psychosocial burden on patients, including anxiety and depression, which significantly diminishes their quality of life. The primary objectives of AF treatment include symptom relief, heart rate and rhythm control, and stroke risk reduction. AF catheter ablation (AFCA) has emerged as the most prevalent cardiac ablation procedure globally and is a critical strategy for rhythm control. However, the long-term prognosis remains unsatisfactory for some patients. Therefore, alongside enhancing the safety and efficacy of AFCA, strategies that improve ablation outcomes through lifestyle interventions and risk factor management are also regarded as vital goals in the management of AF patients.

Educational interventions utilizing videos and comics represent a non-invasive and engaging emerging approach to disease management, aimed at improving patients' emotional well-being, sleep quality, and lifestyle, potentially influencing disease prognosis. Research indicates that animated interventions for patients with acute coronary syndrome can enhance disease awareness, medication beliefs, and prognosis by educating them about their condition and the necessity of procedures or referrals. A randomized controlled trial by Anna et al. demonstrated that among 135 patients requiring coronary angiography, those in the comic illustration group exhibited significantly improved understanding of the procedure and satisfaction, alongside reduced anxiety levels.

Currently, there is limited research focusing on the impact of video interventions on surgical satisfaction, emotional state, and sleep quality in patients undergoing AFCA. This study proposes an innovative strategy for the treatment of AF through video interventions and underscores the necessity of addressing this critical issue in the future management of AF patients. Given the substantial economic burden AF places on the healthcare system in our country, this research aims to further explore

the effects of combined catheter ablation and video interventions on patients' anxiety, depression, medication adherence, and quality of life. We anticipate that this study will advance AF treatment strategies, provide robust support for clinicians, and facilitate patient recovery.

## **Study Rationale**

We used digital animation to educate patients. Digital animation has the characteristics of humor, easy to understand, interesting, and patients are more likely to accept, good adherence and easy to understand. Science education is different from before video, we provide all the digital animation designed by wuhan university people's hospital of professional medical personnel, can fully guarantee the quality of the video content. In addition, we produced a series of popular science videos, including the pathogenesis of AF, surgical methods of AFCA, preoperative preparation and examination of AFCA, postoperative precautions of AFCA, and suggestions for out-of-hospital lifestyle, covering all aspects of patients' onset, treatment and lifestyle. In multi-phase digital animation education mode, we adopted many times means of intervention, since found in patients with disease in hospitalized patients, treatment, discharge, and other key point is to intervene.

Multi-phase digital animation education process accompanied by paramedics offline to complete all the way, in the process of physicians were also responsible for solve doubts, maximize helps people understand and learn animation. The time node of multi-period intervention is the key time point for patients to be confused about the disease, treatment and lifestyle, which exactly needs the communication of doctors to help patients understand, reduce the negative emotions of patients, and improve the degree of medical cooperation and satisfaction of patients. Multi-stage digital animation education mode can help medical staff to complete doctor-patient communication efficiently, conveniently and visually, which is easy for patients to accept and understand. This model to better complete the doctor-patient communication is an important link, can effectively reduce the doctor-patient contradiction. At the same time, it can effectively improve the cognition and

compliance of patients, and improve the satisfaction of patients. It is worth noting that multi-stage digital animation education is only a mode to assist doctors to better complete the doctor-patient communication, and can never replace doctors. Doctors are the main carrier of doctor-patient communication and medical process.

Now, most current medical decision-making focuses only on the patients with disease occurrence, development, ignored the patients related issues. Patients in the hospital during the period of emotions and satisfaction are still part of the treatment process should be the doctor should not be neglected. More time digital animation education model in helping patients at the same time, increase the doctor's working efficiency, reduce the workload. It can improve the participation of patients in the process of disease diagnosis and treatment, help patients better complete medical decision-making, and become the first responsible person for their own health.

## **Study Purpose**

**Primary Objective:** To assess the improvement in quality of life among patients with AFCA three months post-discharge.

**Secondary Objectives:** To evaluate the changes in anxiety, depression, and medication adherence among patients with AFCA three months after discharge.

## **Study Design**

The study is designed to be a randomized, controlled trial conducted to test the therapeutic benefit of multi-stage digital animation education with AF.

Our study was conducted at the Department of Cardiology, Renmin Hospital of Wuhan University, a tertiary academic medical center renowned for its extensive clinical experience in cardiovascular interventional procedures. The hospital's AFCA team specializes in managing complex arrhythmia cases, ensuring comprehensive and high-quality care for patients undergoing AFCA. Potential participants were identified from the hospital's AFCA patient registry, which encompasses all patients with a confirmed AF diagnosis verified by 12-lead ECG or Holter monitoring. Our research team meticulously reviewed electronic health records (EHR) to screen for eligibility based on predefined criteria. Identified patients were approached during

pre-admission consultations or via telephone prior to admission to provide detailed information about the study.

During recruitment contacts, a standardized protocol was strictly followed to ensure that participants were fully informed about the study's purpose, procedures, potential risks, and benefits. Our research team provided a thorough explanation of the intervention (digital animation-based education versus standard care) and addressed any questions. Participants who received this information were invited to sign the informed consent form upon admission. Only those who voluntarily consented were enrolled in the study. Once informed consent was obtained, baseline data were collected to confirm eligibility, including medical history (AF subtype, comorbidities, prior treatments), demographics (age, gender, ethnicity), vital signs (blood pressure, heart rate), and diagnostic results (echocardiogram, Holter monitor). This ensured that all participants met the eligibility criteria before proceeding with randomization.

The recruitment period extended from January 3, 2022, to August 18, 2023. During this time, continuous monitoring for any adverse events was conducted throughout the follow-up period. Both recruitment and follow-up adhered strictly to the ethical guidelines approved by the Institutional Review Board of Renmin Hospital of Wuhan University.

Based on digital animation stage education randomized controlled trial participants were randomly assigned to digital animation intervention group and routine treatment group. In addition to conventional treatment, patients in the intervention group received multi-period digital animation education. Firstly, the animation education for patients during hospitalization mainly focused on the pathogenesis and harm of AF. Secondly, animation education for patients after hospitalization focused on the treatment and prognosis of AF. Thirdly, animation education related to preoperative preparation and precautions was carried out before surgery. Then, the digital animation education for patients after surgery mainly focused on postoperative nursing and postoperative precautions. Finally, animation education about post-discharge medicine and life advice was carried out for patients

before discharge. Patients in the control group only received conventional treatment. The routine treatment of patients in the intervention group and the control group was strictly carried out in accordance with the guidelines for AF.

Participate in the intervention group and control group patients were age, gender, history, height, weight, smoking, alcohol and other baseline data collection, in addition, in intervention group and control group of patients admitted to hospital at the same time completed the self-rating anxiety scale [SAS]; self-rating depression scale [SDS]; the quality of life in patients with atrial fibrillation [AF-QoL-18]; medication adherence report scale [MARS5]. The patients were followed up by telephone at 3 months after discharge, and the SAS, SDS, AFQ-18 and MARS5 were collected again. At the same time, the patients were followed up for 3 months after discharge, including daily exercise, smoking, drinking, staying up late, and changes in dietary habits.

### **Study Duration**

Participants were required to receive the intervention throughout their hospital stay and to be followed up at 3 months after discharge.

### **Study Population**

The randomized controlled trial included 208 AF patients who underwent AFCA in the Department of Cardiology at Renmin Hospital of Wuhan University from January 2022 to August 2023. Main inclusion criteria were as follows: (1) Age between 18 and 90 years old; (2) Confirmed diagnosis of AF by surface electrocardiogram or ambulatory electrocardiogram examination; (3) AF patients who underwent successful RFA during hospitalization at Wuhan University People's Hospital. The diagnosis and treatment criteria for AF strictly followed the guidelines for AF management. Participants who were unable to comply with the study (as determined by clinical researchers) or who had a history of cardiac surgery (including percutaneous coronary intervention, coronary artery bypass grafting (CABG), or heart transplantation) were excluded.

### **Inclusion and exclusion criteria.**

---

**Inclusion criteria**

---

Age between 18 and 90 years old

Confirmed diagnosis of AF by surface electrocardiogram or ambulatory electrocardiogram examination

AF patients who underwent successful AFCA during hospitalization at Wuhan University People's Hospital

---

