Based on digital animation science auxiliary medical personnel to complete the doctor-patient communication during the patient in the hospital. Doctor-patient communication is an important part of medical decision-making, which affects the prognosis of patients and runs throughout their hospitalization. Efficient and warm doctor-patient communication can effectively reduce medical conflicts and improve patient satisfaction, so as to quickly implement treatment in the occurrence and development of patients' diseases. Based on digital animation mode of doctor-patient communication more efficient, help patients quickly realize his illness, actively cooperate with treatment.

We developed a series of four animation videos for patients, each tailored to different stages of their care: upon admission, preoperatively, postoperatively, and at discharge. The production of these animations was funded by the Department of Cardiology at Renmin Hospital of Wuhan University, which holds the intellectual property rights. Currently, public access to these animations is restricted. However, we recognize their potential value to a broader audience and are considering further optimizations to facilitate wider dissemination in the future.

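### Successful ablation is an inclusion criterion, but it cannot be known at randomisation, and the visible text defines no analysis set that keeps randomised patients who fail it

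*Combined protocol and SAP*

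**What the plan says.** **The criterion.** The Inclusion criteria table requires "AF patients who underwent successful AFCA during hospitalization". Study Population repeats the rule with a different abbreviation: "AF patients who underwent successful RFA during hospitalization at Wuhan University People's Hospital". Neither section defines success.

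**Timing of eligibility.** Study Design describes the consent step as follows: "Participants who received this information were invited to sign the informed consent form upon admission". Baseline data (history, demographics, vital signs, echocardiogram, Holter) are then collected, and the section concludes: "This ensured that all participants met the eligibility criteria before proceeding with randomization".

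**Timing of the intervention.** Intervention Strategy describes four animations, "each tailored to different stages of their care: upon admission, preoperatively, postoperatively, and at discharge". Study Design also places one education session ahead of surgery.

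**Analysis.** Statistical Method compares the change from baseline to 3 months between arms by an independent t-test, with significance at p < 0.05. It names no analysis population and gives no rule for a randomised patient without a successful ablation.

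**Context.** Under Blinding, nobody is blinded. Intervention Strategy expects the animations to make patients cooperate more actively with treatment. Study Population gives 208 patients who underwent ablation, and Randomization gives the same 208 as the number allocated.

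**The concern.** An inclusion criterion should be decidable before allocation. This one depends on an event after allocation, and in the intervention arm after two of the four animations. If it is enforced, the analysed groups are no longer the randomised groups. They are those among them who went through with the procedure and were judged to have had a successful one.

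That matters if the filter works differently by arm. The protocol hopes that the animations will improve cooperation with treatment, and proceeding to ablation is one form of cooperation. Clinicians who know the allocation decide whether the procedure goes ahead, and success has no written definition. The outcomes are self-reported quality of life, anxiety, depression and adherence. Patients who withdraw from a procedure may well score differently on these scales from those who proceed. An analysis confined to successful ablations could then show a difference, or hide one, for reasons unrelated to the effect of the education on the outcome.

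**Working it through.** **Step 1: the order of events.**

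| Event | Source | When |
|---|---|---|
| Consent, baseline data, eligibility confirmed | Study Design | On admission, before randomisation |
| Randomisation | Study Design; Randomization | After eligibility; exact moment not stated |
| First two animations (intervention arm) | Intervention Strategy; Study Design | Admission and before surgery |
| Ablation, success or failure known | Inclusion criteria; Study Population | After the pre-operative animation |

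The moment of randomisation is an inference, but a forced one: only the intervention arm receives the animations, so the arm must be known before the first is shown. Three statements therefore cannot all hold: all criteria met before randomisation, successful ablation as a criterion, and animations before surgery.

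**Step 2: what the counts show.** The documents give 208 both as the number allocated and as the number who underwent ablation. This fits with no removals, and also with a description written after removals or replacements. It settles neither.

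**Step 3: effect on numbers.** The plan's own figures are 80 assessable patients per group and 80% retention. The 80 cannot be uniquely reproduced, because no control proportion is given, but this point does not depend on it. With 208/2 = 104 per arm:

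- No removals: 104 × 0.80 = 83.2 assessable per arm.
- With a fraction q removed, on top of the 20% attrition: 104 × (1 − q) × 0.80. Assumed q of 2%, 5% and 10% gives 81.5, 79.0 and 74.9.
- The 80 is reached at q = 1 − 100/104 = 3.8%.

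**Step 4: possible bias.** The documents give no loss rates, so all rates here are assumptions.

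*(a) Equal, non-differential loss.* The same kind of patient is removed at the same rate in both arms. The shift is 0.

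*(b) Loss of 10% in control and 5% in intervention*, the removed patients' change being D SD worse. The intervention arm keeps patients whom the control arm would have removed, so the shift has size D × (q0 − q1)/(1 − q1):

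- D = 0.5: 0.5 × 0.05/0.95 = 0.026 SD.
- D = 1.0: 1.0 × 0.05/0.95 = 0.053 SD.

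*(c) Loss of 10% in one arm and none in the other*, with removal of the extreme tenth on a trait correlated 0.5 with the analysed outcome. The shift is 0.5 × φ(z)/(1 − q), where z is the 10% normal quantile: 0.5 × 0.1755/0.90 = 0.5 × 0.195 = 0.097 SD.

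**Step 5: consequence for the test.** At 80 per arm the standard error is √(2/80) = 0.158 SD. The two-sided 5% error rate under a bias b is P(Z > 1.96 − b/0.158) + P(Z < −1.96 − b/0.158).

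| Scenario | Bias (SD) | Type I error |
|---|---|---|
| (a) | 0 | 5.0% |
| (b), D = 0.5 | 0.026 | 5.3% |
| (b), D = 1.0 | 0.053 | 6.3% |
| (c) | 0.097 | 9.5% (9.7% at 0.10 SD) |

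**The case against.** The strongest reply is that nothing went wrong in practice. No section says that anyone was removed. Candidates came from the hospital's ablation registry, and Randomization describes them as patients undergoing the procedure, so cancellations may have been rare. The past-tense criterion may simply describe the final sample. The flowchart, where exclusions after randomisation would normally appear, is not reproduced in the text available. All this stands, and it limits the point to what the rule would do if followed and to the absence of a stated safeguard.

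Four stronger readings are tempting, and the documents do not support them.

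- *Patients were in fact removed after randomisation.* A reader might infer this from the criterion and the matching counts of 208. The counts are equally compatible with no removals.
- *The animations change who is ablated.* Study Rationale says they should "help patients better complete medical decision-making", but that is general rationale. No section says that they affect whether an ablation takes place or succeeds. Dependence on arm is a risk here, not a finding.
- *The exclusion of patients unable to comply is a second filter after randomisation.* Study Population lists it beside previous cardiac surgery, the exclusion table has a matching suitability item, and Study Design says eligibility was settled before allocation. It reads as a screening judgement. Nor does Study Duration say that only the intervention arm had anything to comply with; control patients also had scales to complete.
- *The type I error is about 10%.* That is scenario (c), which assumes loss in one arm only and strict selection. Milder assumptions give 5.0% to 6.3%. If the trait acts mainly on the level of quality of life, the analysis of change from baseline would remove part of the bias.

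**Conclusion.** The concern holds as a defect in the written rule. The criterion cannot be assessed when the protocol says it was. Enforcing it would exclude randomised patients on a later event, and the visible text sets out no analysis of all randomised patients to prevent this. That conclusion needs no assumed figure; it rests only on the inference that allocation precedes the first animation.

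Whether any patient was lost this way, and in which direction a bias would run, cannot be determined. The plausible size is 0 to about 0.10 SD, on assumed loss rates throughout. The upper end needs a 10% selective loss confined to one arm. The point deserves correction because it decides who is in the primary comparison, and not because a large bias has been shown.

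**What to change.** 1. In Inclusion criteria and Study Population, define eligibility as scheduled for AFCA at the time of randomisation, and use the same procedure term in both places.
2. In Statistical Method, state that the primary analysis includes every randomised patient in the allocated arm, whatever the ablation result.
3. Report by arm, with reasons, everyone randomised who did not have a successful ablation, including a statement if there were none.
4. If anyone was removed, restore those whose outcome data exist and treat the others as missing data.
5. Keep the successful-ablation subset as a sensitivity analysis, labelled as conditioned on an event after randomisation.

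**Cost.** Mainly wording and a count from the randomisation log. Including patients without a successful ablation may dilute the effect slightly. Recruitment is described as having run from January 2022 to August 2023, so new 3-month calls cannot be assumed feasible, and some outcomes may stay missing. If the log shows that nobody was removed, items 1 to 3 suffice.

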**Exclusion criteria**

---

Previous cardiac surgery

Out of age

Refusal to sign consent form

Mental abnormality

Not suitable for participation

---

**Early termination of the study**

This study may be temporarily suspended or terminated early if there is good and reasonable cause for such termination.

| Suspended or terminated criteria                                        |
|--------------------------------------------------------------------------------|
| Determination of unexpected, significant or unacceptable risks to participants |
| Identify patients who may be at risk for an Serious Adverse Events(SAE)        |
| Inadequate compliance with protocol requirements by the investigator           |

**Interim analyses**

No interim analyses were planned or conducted.

**Screening, Randomization, and Follow-up Flowchart**

[figure not shown]

## Study Procedures

### Intervention Strategy

The main purpose of multi-stage digital animation education is to carry out popular science intervention for patients with AF based on the Chinese real estate management guidelines, improve patients' cognition of AF disease, help patients relieve their bad emotions during hospitalization, change the bad living habits of patients and even healthy people, and prevent and reduce the risk factors inducing AF. Intervention will continue in all patients during hospitalization, intervention content mainly includes: 1) monitoring the quality of life of AF patients; 2) monitoring in patients with AF patients hospitalization anxiety; 3) monitor the depression of patients during hospitalization; 4) to improve patients' medication compliance.

So far, clinical treatment revolves around the pathophysiology of the patient's disease, and often ignores the patient's psychological problems, including but not limited to anxiety, depression and other negative emotions. Patients with anxiety, depression, bad mood and mental illness, unknown, worry about prognosis and

surgical risk for the disease had close relations, etc. To assess patients with anxiety, depression, bad mood, you first need an objective solution to uniform standards.

Establish a popular science mode based on digital animation. Digital animation is a new, humorous, portable and easy-to-understand media video. Popular science education has been shown to improve the cognition to the disease, patients improve patient adherence and assist patients to establish a good way of life, reduce disease risk factors. Ever more popular science education depends on form of text, images, content is relatively dry, less patient acceptance and understand the degree of difference. The popular science mode based on digital animation is vivid, vivid, humorous and interesting, which is easy for patients to understand and deepen their learning degree of popular science content.

Based on digital animation science auxiliary medical personnel to complete the doctor-patient communication during the patient in the hospital. Doctor-patient communication is an important part of medical decision-making, which affects the prognosis of patients and runs throughout their hospitalization. Efficient and warm doctor-patient communication can effectively reduce medical conflicts and improve patient satisfaction, so as to quickly implement treatment in the occurrence and development of patients' diseases. Based on digital animation mode of doctor-patient communication more efficient, help patients quickly realize his illness, actively cooperate with treatment.

We developed a series of four animation videos for patients, each tailored to different stages of their care: upon admission, preoperatively, postoperatively, and at discharge. The production of these animations was funded by the Department of Cardiology at Renmin Hospital of Wuhan University, which holds the intellectual property rights. Currently, public access to these animations is restricted. However, we recognize their potential value to a broader audience and are considering further optimizations to facilitate wider dissemination in the future.

